### Randomisation and blinding

Pregnant women will be randomly assigned to the order in which they receive the three MMS formulations in the crossover trial. Pregnant women will be randomised in a 1:1:1:1:1:1 ratio to one of six treatment sequence orders to receive the three MMS formulations first, second or third in order (eg, 30, 45, then 60 mg; or 45, 30, then 60 mg; or 45, 60, then 30 mg, etc.) as shown in table 1. The allocation sequence will be generated by two non-study staff at George Washington University through computer-generated randomisation lists that will be block randomised (block sizes of 6). An independent study pharmacist will privately prepare a set of three MMS blister packs with participant identification numbers (IDs) according to the allocated treatment sequence. At the randomisation visit, research staff will assign pregnant women to the next available participant ID, which corresponds to a set of three prelabelled blister packs. Participants will receive an MMS blister pack at baseline, month 1 and month 2 visits. No washout period will be included between crossover periods. These randomisation procedures will ensure treatment allocation is fully concealed. Furthermore, the trial is quadruple-blind since the participants, investigators, outcome assessors and data analysts will be blinded to the participant treatment sequence.

**Table 1 T1:** Multiple micronutrient supplementation treatment sequences in the crossover design

Regimen sequence	Month 1	Month 2	Month 3
Sequence 1	30 mg	45 mg	60 mg
Sequence 2	30 mg	60 mg	45 mg
Sequence 3	45 mg	30 mg	60 mg
Sequence 4	45 mg	60 mg	30 mg
Sequence 5	60 mg	30 mg	45 mg
Sequence 6	60 mg	45 mg	30 mg

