### Sample size

This study is powered for the acceptability (positive impression per Likert scale) of MMS using a non-inferiority design. An empirical estimate of the SD is 0.76 based on real data from the non-inferiority of low-dose compared with standard high-dose calcium supplementation in pregnancy trial.^19^ Therefore, allowing for a non-inferiority margin of 0.5 point difference, 90% power and an alpha of 0.025 to accommodate two statistical tests for 60 versus 30 mg MMS and 45 versus 30 mg MMS (0.05/2), we would require a total of 147 women. To account for ~5% of missing or incomplete data (fetal loss, withdrawal etc.), we will therefore recruit 26 women for each of the six treatment sequences. Thus, the total sample size will be 156 participants.

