Preference between two doses (45 mg vs 30 mg, and 60 mg vs 30 mg) will be analysed using the win ratio method to determine the preferred dose among each dose pair based on the preference of each participant. We collected the participants’ preferences for MMS formulations with 30 mg, 45 mg or 60 mg of iron by asking which supplement they liked the most or the least after taking all three MMS formulations. Take the 30 mg vs 60 mg comparison as an example. Logistic regression will be employed to estimate the probability that the 30 mg regimen is the preferred one among the two regimens for a specific woman, adjusting for differences in the periods of the 30 mg regimen and the 60 mg regimen, as well as the sequence of the three regimens (six sequences in total using five binary indicators). The sample size will be the number of pregnancies that received both the 30 mg and the 60 mg formulation. We will report the point estimate and 95% CIs for the percentage of participants favouring the 30 mg method as the winner. If the preference is not different between the 60 mg and the 30 mg formulations, the percentage of pregnancies choosing the 30 mg regimen as the winner should equal 50%. Similar analyses will be performed to compare 45 mg versus 30 mg.

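### The preference model enters the period difference alongside five sequence indicators that already determine it, so the stated period adjustment cannot be estimated and the reported percentage is left undefined

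*Protocol article*

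**What the plan says.** The Statistical analysis section of the protocol article names the model and its target: "Logistic regression will be employed to estimate the probability that the 30 mg regimen is the preferred one among the two regimens". It lists two adjustments in that one model. The first is "adjusting for differences in the periods of the 30 mg regimen and the 60 mg regimen"; the second is "as well as the sequence of the three regimens (six sequences in total using five binary indicators"). The same approach is to be used for 45 vs 30 mg.

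The output is also stated: "We will report the point estimate and 95% CIs for the percentage of participants favouring the 30 mg method as the winner". With no difference in preference, "the percentage of pregnancies choosing the 30 mg regimen as the winner should equal 50" per cent. The text does not say how the percentage is obtained from the fitted model.

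Under Randomisation and blinding, each woman is allocated to "one of six treatment sequence orders" in equal ratio, and Table 1 lists all six orders of the three doses. The Sample size section gives the numbers: "we will therefore recruit 26 women for each of the six treatment sequences". The most and least preferred formulations are secondary outcomes (Outcomes, Table 2).

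**The concern.** In the linear mixed and GEE models elsewhere in the section, each woman contributes three records and there is a treatment term, so sequence and period can both be fitted. The preference model differs. It has one record per woman per dose pair and no treatment covariate, and a woman's sequence fixes the periods in which she took the two doses. An intercept and five indicators already use up all the information in six sequences, which leaves nothing from which to estimate a period coefficient.

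At stake is whether the preference result is fixed in advance. Software given this model will stop, or will discard a column by its own rule. The coefficients, and the intercept in particular, then mean different things depending on column order and reference level. A period effect on preference cannot be ruled out: there is no washout, and women are followed for three months of advancing pregnancy. Under one of the possible parameterisations such an effect would look like a dose preference when set against the 50% null.

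**Working it through.** **Inputs.** The six sequences come from Table 1. There are 26 women per sequence (Sample size), and 6 × 26 = 156 reproduces the stated total. The only figure the plan attaches to the preference analysis is the 50% null. The size of a period effect on preference is not in the documents. I assume β = 0, 0.2 or 0.4 log-odds per month, linear in the period difference d and favouring the later dose.

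**Step 1: period differences.**

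| Sequence | Period of 30 mg | Period of 45 mg | Period of 60 mg | d, 30 − 60 | d, 30 − 45 |
|---|---|---|---|---|---|
| 1 | 1 | 2 | 3 | −2 | −1 |
| 2 | 1 | 3 | 2 | −1 | −2 |
| 3 | 2 | 1 | 3 | −1 | +1 |
| 4 | 3 | 1 | 2 | +1 | +2 |
| 5 | 2 | 3 | 1 | +1 | −1 |
| 6 | 3 | 2 | 1 | +2 | +1 |

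**Step 2: collinearity.** Take sequence 1 as reference and let S2 to S6 be the indicators.

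- 30 vs 60 mg: d = −2 + S2 + S3 + 3·S4 + 3·S5 + 4·S6, exactly.
- 30 vs 45 mg: d = −1 − S2 + 2·S3 + 3·S4 + 0·S5 + 2·S6, exactly.

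Intercept, d and five indicators make 7 columns with rank 6 for both pairs. Coding d as categories gives 1 + 3 + 5 = 9 columns, still rank 6.

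**Step 3: percentage read from the intercept (30 vs 60 mg, no dose preference).** The true log-odds in each sequence is then β·d.

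- *Period term dropped, sequence 1 as reference.* The intercept is the sequence 1 log-odds, and expit(−2β) gives 50.0%, 40.1% and 31.0% for β = 0, 0.2 and 0.4. It rests on 26 women, with a 95% CI half-width near 50% of 1.96 × √(0.25/26) ≈ 19 points. Over the choice of reference sequence, the value runs from 40.1% to 59.9% (β = 0.2) or from 31.0% to 69.0% (β = 0.4).
- *Period term kept, sequence 6 indicator dropped.* Sequence 1 gives a − 2b and sequence 6 gives a + 2b, so a is the mean of the two log-odds: (−2β + 2β)/2 = 0, or 50.0% for every β. It rests on two sequences. At β = 0 its variance is ¼ × 2/(26 × 0.25) = 0.077, so the SE is 0.277 and expit(±1.96 × 0.277) is about 37% to 63%.

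**Step 4: predictions averaged over sequences.** Every full-rank version gives the same six fitted probabilities. For β = 0.4 the equally weighted mean is (31.0 + 40.1 + 40.1 + 59.9 + 59.9 + 69.0)/6 = 50.0%. It is also 50.0% for β = 0 and 0.2. Because the model is saturated by sequence, weighting by the women analysed gives Σyₛ/N, the raw proportion. The period term does not change this estimate.

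**Step 5: intercept and period difference only.** The rank is 2 of 2. Under no dose preference, expit(intercept) is 50.0% for all three values of β. With 156 women the half-width is about 1.96 × √(0.25/156) ≈ 8 points, so the 95% CI is about 42% to 58%.

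**The case against.** A reader might infer that the reported percentage will be wrong, because the intercept is the only place for the preference effect and it describes a single reference sequence. The documents do not support that reading, for three reasons.

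- The article never mentions the intercept. It promises a percentage of participants, which is at least as naturally an average over the women. Read so, the collinearity does no harm: with six equal sequences the average is 50% under the null and uses all 156 women. The unseen analysis plan may say exactly this.
- Even an intercept belongs to one sequence only if the period term is the column discarded. The article lists the period difference first. If columns enter in that order and the last redundant one goes, the intercept is 50% under a linear period effect. It is imprecise but not biased by that effect.
- The 40% and 31% need four things together: the period term dropped, sequence 1 as reference, the intercept reported, and a period effect whose size the documents do not give. With no period effect the same intercept gives 50%.

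These points stand and limit the finding, but they do not remove it. The article fixes the covariates down to the number of indicators, so this is not a detail left open. No analysis plan can carry out that sentence as written; it has to depart from it. On the harmless reading, the stated period adjustment does nothing to the estimate.

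**Conclusion.** The preference model is over-parameterised as specified, for both dose pairs. This is exact algebra from Table 1 and needs no assumption beyond one preference per woman per pair. The period adjustment cannot be estimated beside the five sequence indicators, and the article does not define a percentage that is independent of how the software resolves the redundancy.

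The size of the problem depends on what is reported. For 30 vs 60 mg with no dose preference, an intercept could show anything from 31% to 69% at an assumed 0.4 log-odds per month, from 40% to 60% at 0.2, and 50% at 0. An average over balanced sequences shows 50% throughout. It is therefore not established that the published figure would be biased; it is established that the written plan does not determine the figure. Preference is a secondary outcome, and the primary acceptability analysis and the sample size are not touched.

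**What to change.** Choose one of two forms, for both dose pairs, and state it before unblinding.

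- **Period difference only.** Drop the five sequence indicators and fit logit P(30 mg preferred) = intercept + b × (period of 30 mg − period of the comparator). Report expit(intercept) with its 95% CI. The covariate is symmetric about zero across the six sequences, so this is the period-adjusted preference from all women.
- **Sequence only.** Keep the indicators, omit the period term, and report the equally weighted average of the six sequence-specific probabilities with a delta-method or bootstrap CI. Equal weights also prevent unequal loss across sequences from shifting the result, which a raw proportion would not.

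Away from the null the two differ slightly. With a true dose log-odds of 0.4, the first targets expit(0.4) = 59.9%, while the second gives 59.9%, 59.7% or 59.2% for period effects of 0, 0.2 or 0.4. The plan should therefore name which one is reported.

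The cost is one sentence in the analysis plan, with no change to data collection, sample size or participants. By the article's dates, follow-up runs to late June 2026 and analysts are blinded to sequence, so the change can be made without knowledge of results.

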**Figure 1 F1:**
[figure not shown]
Schedule of enrolment, interventions and assessments in MID-ACT. MID-ACT, Multiple Micronutrient Supplementation (MMS) Iron Dose Acceptability Crossover Trial, FACIT, Functional Assessment of Chonic Illness Therapy - Fatigue Scale

At the month 2 and month 3 follow-up visits, participants will be asked to compare the formulation taken during the current month with the MMS taken in the preceding month and to indicate any perceived differences or preferences. At the month 3 discharge visit, participants will be asked to reflect on all three MMS formulations and to report whether they perceived any differences among them, as well as whether they preferred or disliked any formulation relative to the others. Participants will also be asked to guess the order in which they received the MMS formulations by iron dose (eg, 30 mg first, 60 mg second, 45 mg third).

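### The preference analysis pairs a denominator of all women who received both doses with a 50% no-difference value; the two agree only if no woman leaves the pair unordered

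*Protocol article*

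**What the plan says.** The Statistical analysis section of the protocol article says that preference for 45 mg versus 30 mg and for 60 mg versus 30 mg "will be analysed using the win ratio method to determine the preferred dose among each dose pair". The data come from "asking which supplement they liked the most or the least after taking all three MMS formulations". Taking 30 mg versus 60 mg as its example, the section then fixes three things:

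- **Outcome.** "Logistic regression will be employed to estimate the probability that the 30 mg regimen is the preferred one among the two regimens", so the response is binary.
- **Denominator.** "The sample size will be the number of pregnancies that received both the 30 mg and the 60 mg formulation".
- **No-difference value.** If preference does not differ, "the percentage of pregnancies choosing the 30 mg regimen as the winner should equal 50" per cent.

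For reporting: "We will report the point estimate and 95% CIs for the percentage of participants favouring the 30 mg method as the winner". The 45 mg versus 30 mg comparison is to be handled similarly.

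Under Data collection (text below Figure 1), women at the month 3 visit are asked "to report whether they perceived any differences among them, as well as whether they preferred or disliked any formulation relative to the others".

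**The concern.** The denominator is defined by what a woman received, not by whether she ranked the two doses. A 50% no-difference value is right for a binary outcome only if each woman in the denominator picks one dose or the other. The month 3 questions leave room for women who do neither, and the Interventions section makes such answers plausible because the tablets are manufactured to be indistinguishable.

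An unordered pair can also arise without a no-preference answer. A woman who names both a most-liked and a least-liked formulation orders all three doses. A woman who names only one, and names 45 mg, says nothing about 30 mg against 60 mg.

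Any distortion would run one way. The reported figure is the share favouring 30 mg, so ties kept in the denominator pull it below 50% and could be read as a preference for more iron. The Discussion says the findings are meant to inform programmes moving to lower-dose iron, so the misreading would bear on the question the trial serves.

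**Working it through.** **Inputs.** The 50% value, the denominator and the 95% level come from Statistical analysis. N = 147 is the evaluable number in Sample size; the total recruited is 156. The tie share t (women whose answers do not order the pair) is not given and is assumed over a range.

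**Step 1: the plan's own figure.** With no dose preference, women who order the pair split evenly. If the others are kept and counted as not choosing 30 mg, the expected share is p = (1 − t)/2. At t = 0 this gives 50%, the plan's value. At any t above 0 it is lower; for example, at t = 20%, p = 0.80/2 = 40%.

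**Step 2: when the interval lies wholly below 50%.** With N = 147, a Wilson 95% interval lies below 50% when the observed share is under 0.5 − 1.96 × √(0.25/147) = 0.5 − 0.081 = 0.419. That is 61 women or fewer, since 147 × 0.419 = 61.6.

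**Step 3: how often that happens.** The exact binomial probability of 61 or fewer out of 147, without covariates, is as follows. A logit-Wald interval gave the same results.

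| Assumed tie share t | Expected 30 mg share | P(95% CI wholly below 50%) |
|---|---|---|
| 0% | 50.0% | 2.4% |
| 5% | 47.5% | 8.4% |
| 10% | 45.0% | 22% |
| 20% | 40.0% | 68% |
| 30% | 35.0% | 96% |

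Normal check at t = 10%: mean 147 × 0.45 = 66.15, SD √(147 × 0.45 × 0.55) = 6.03, z = (61.5 − 66.15)/6.03 = −0.77, probability about 22%. With N = 156 the figures at 10%, 20% and 30% ties are about 23%, 70% and 97%.

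**Step 4: a real preference can be hidden.** Suppose 45% prefer 30 mg, 25% prefer 60 mg and 30% are tied. The share over all recipients is 45%. Among women who order the pair it is 45/70 = 64%.

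**Step 5: after restriction to ordered pairs.** From 147 women, tie shares of 10%, 20%, 30% and 50% leave 132, 118, 103 and 74. The chance of an interval wholly below 50% is then 2.2%, 2.6%, 2.4% and 2.4%. Scoring a tie as half a win and keeping everyone gives about 2.5% to 2.7% by simulation at tie shares of 10%, 30% and 50%.

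**The case against.** A reader might infer that the planned test will falsely show 30 mg losing. The article does not support that. Nowhere does it say that a woman without a preference is coded as not choosing 30 mg. The method it names, the win ratio, compares wins with losses and ordinarily leaves ties out of both, in which case 50% is the right value. The sample-size sentence can be read as saying only who can inform a pairwise comparison, so that women lost before receiving both doses are excluded. The most-liked and least-liked items may also be forced choices; the questionnaire is not shown. If every woman answers both, no pair is left unordered. Finally, a tie rule is something an analysis plan commonly supplies, so its absence from a condensed article is no finding.

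Most of this stands, and it makes the point conditional. What it does not remove is the mismatch in the stated text. If ties are dropped, the analysed number is no longer everyone who received both doses. If everyone is kept in the binary model, 50% is no longer the no-difference value. The complete-case sentence in Statistical analysis does not settle it: it is limited to primary analyses, and a no-preference answer is an observed response rather than a missing one.

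**Conclusion.** The stated denominator and the stated no-difference value are compatible only if ties are absent or excluded, and the data collection described does not ensure either. The size of the problem depends on two things the article leaves open: the tie share, and whether tied women stay in the denominator as not choosing 30 mg. If they do, the false-loss rate is about three times nominal at 5% ties and close to certain from about 30%. No figure in the article supports a particular tie share.

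Severity is moderate. Preference is a secondary outcome with no decision rule attached beyond an estimate and its interval. It would be wrong to infer that the main conclusion is at risk: the sample size and the non-inferiority tests rest on the Likert score, which this does not touch.

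**What to change.** Change the sample-size sentence so that each pairwise analysis includes women who received both doses and whose answers order that pair. Test that share against 50%. Report the number and share of ties for each comparison. Add a sensitivity analysis that keeps all women who received both doses and scores a tie as half a win, for which 50% remains the no-difference value.

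The cost is a few sentences and some precision. At 30% ties the approximate 95% half-width around 50% grows from 0.98/√147 = 8.1 percentage points to 0.98/√103 = 9.7. No new data are needed. The article gives late June 2026 as the expected end of follow-up and says the analysts are blinded to sequence, so the rule can be fixed before unblinding.

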## Ethics and dissemination

The MID-ACT protocol was approved by Harvard T. H. Chan School of Public Health Institutional Review Board (IRB) (Ref. No. IRB22-1581), the Ifakara Health Institute IRB (IHI/IRB/No.: 45–2023), the Muhimbili University of Health and Allied Sciences IRB (MUHAS-REC-07–2023-1801), the National Health Research Ethics Committee (Ref. No. NIMR/HQ/R.8a/Vol. IX/4448), Tanzania Commission for Science and Technology (Permit No. CST00000303-2024–2024-00342) and the Tanzania Medicine and Medical Device Authority (Ref No. BC.69/96/98/01). The George Washington University and Beth Israel Deaconess Medical Center IRBs relied on the Harvard IRB. All participants will provide written informed consent before enrolment into the trial and will have the right to withdraw at any time. All protocol modifications will be submitted to the trial IRBs for approval prior to implementation. Updates will also be made to the clinical trial registry, and approved amendments will be communicated to the study staff and to participants if relevant to participation or safety. An independent, external study monitor will conduct ongoing trial monitoring to ensure protocol compliance and data integrity.

In terms of dissemination, we will share the primary and secondary findings of our trial through publications in peer-reviewed journals and presentations at conferences, research seminars, and scientific meetings. We will work with the Healthy Mothers Healthy Babies Program hosted by the Micronutrient Forum to consider any other public-facing dissemination activities. Additionally, we will communicate our results to relevant government and non-governmental stakeholders, including the Tanzania Ministry of Health and Social Welfare and the Tanzania Food and Nutrition Centre, through the distribution of publications and an in-person dissemination meeting.

## Discussion

Our trial will provide causal evidence on maternal acceptability, side effects, adherence, and preferences, as well as robust qualitative data to contextualise and understand women’s experiences taking MMS with different iron doses. The trial findings are intended to inform public health programmes that are switching from higher to lower dose iron-containing supplements in pregnancy. In addition, we are conducting an ongoing efficacy trial to assess the clinical effect of MMS containing 30 mg, 45 mg and 60 mg on maternal anaemia and important perinatal outcomes (clinicaltrials.gov Identifier: NCT06079918).^21^ We will also conduct a crossover trial that will compare IFA containing 60 mg of iron with MMS containing 30 mg of iron to assess the total effect of the difference in iron dose and additional micronutrients on maternal acceptability (clinicaltrials.gov Identifier: NCT06069856). Taken together, these trials will provide robust evidence to inform decision-making regarding the transition from IFA to MMS in settings with a high anaemia burden.
